#### Secondary analysis

An ANCOVA will be used to compare the changes of secondary outcomes after 12 weeks of treatment among groups. Paired *t*-tests will be used to analyze internal variation of the results obtained at week 12 compared to those obtained at baseline in each group. A repeated-measures analysis of variance will be performed to analyze changes per visit in each group.

### Adverse events

All undesirable medical findings that have not been observed prior to the clinical trial will be classified as adverse events. All unexpected responses related to Mecasin and riluzole will be recorded. If serious adverse events occur, these will be notified to the sponsor, Hanpoong Pharm and Foods Co., the Institutional Review Board (IRB), and the Ministry of Food and Drug Safety. The number of adverse events in the two Mecasin groups will be compared using the χ^2^ or Fisher’s exact tests.

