**Methods:**

This is a phase II-A, multi-center, randomized study with three arms. Thirty-six patients with ALS will be randomly assigned to one of three groups, each receiving the standard treatment with 100 mg of riluzole in addition to one of 1.6 g of Mecasin, 2.4 g of Mecasin, or a placebo. The Primary outcome is the Korean version of the Amyotrophic Lateral Sclerosis Functional Rating Scale-Revised result after 12 weeks of treatment. Secondary outcomes include results of the Short Form Health Survey-8, Medical Research Council Scale, Visual Analogue Scale for Pain, Hamilton Rating Scale for Depression, Fatigue Severity Scale, Patient Global Impression of Change, pulmonary function test, forced expiratory volume in 1 s and its ratio to forced vital capacity, creatine kinase, and body weight. The frequencies of total adverse events and serious adverse events will be described and documented. The trial protocol has been approved by the Institutional Review Board of the Wonkwang University Gwangju and Sanbon Hospital (2016–5-4 and 2016–34-01, respectively). An Investigational New Drug status (30731) was granted by the Korea Food and Drug Administration.

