**Fig. 2 Fig2:**
[figure not shown]
The SPIRIT trial schedule of enrolment, intervention, and assessment. *K-ALSFRS-R* Amyotrophic Lateral Sclerosis Functional Rating Scale-Revised, *SF-8* Short Form Health Survey 8, *MRC* Medical Research Council scale for muscle strength, *mMRC* Modified Medical Research Council Scale for Dyspnoea, *VAS* Pain Visual Analogue Scale for Pain, *HRSD* Hamilton Rating Scale for Depression, *FSS* Fatigue Severity Scale, *PGIC* Patient Global Impression of Change

**Table 1 Tab1:** Schedule of study procedures

	Screening	Treatment and evaluation				
		Baseline			Final	
Visit	Visit 1	Visit 2	Visit 3	Visit 4	Visit 5	Follow-up
Schedule	Week −4 to Day 0	Week 0	Week 4	Week 8	Week 12	Week 16
Informed consent	✓					
Demographic characteristics	✓					
Medical history	✓					
Inclusion/Exclusion criteria	✓					
Chest x-ray	✓					
Pregnancy test	✓				✓	
Electrocardiogram	✓				✓	
Randomization		✓				
Medications	✓	✓	✓	✓	✓	
Vital sign	✓	✓	✓	✓	✓	
Body weight	✓	✓	✓	✓	✓	
Pulmonary function test (FEV_1_/FVC)	✓	✓	✓	✓	✓	
Blood tests^a^	✓	✓	✓	✓	✓	
K-ALSFRS-R	✓	✓	✓	✓	✓	
Short Form Health Survey 8		✓	✓	✓	✓	
Medical Research Council Scale for muscle strength		✓	✓	✓	✓	
Visual Analogue Scale for Pain		✓	✓	✓	✓	
Measurement of Muscular Atrophy		✓	✓	✓	✓	
Hamilton Rating Scale for Depression		✓	✓	✓	✓	
Fatigue Severity Scale		✓	✓	✓	✓	
O_2_ saturation and CO_2_ pressure test		✓	✓	✓	✓	
Provision/collection of test medication and placebo		✓	✓	✓	✓	
Adverse events assessment			✓	✓	✓	✓
Patient Global Impression of Change					✓	

^a^Blood (5 mL) will be collected from each patient to measure creatine kinase and other markers

*K-ALSFRS-R* Amyotrophic Lateral Sclerosis Functional Rating Scale-Revised

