#### Exclusion criteria

The exclusion criteria are (1) patients with ≤ 30% forced vital capacity; (2) patients with other neurological diseases, including fronto-temporal dementia with communication difficulties and Parkinson’s disease; (3) patients with cardiovascular disease, including ischemic heart disease; (4) patients with hepatic diseases such as hepatic cirrhosis, hepatic cancer and active hepatitis, or aspartate transaminase/alanine transaminase greater than three times the upper normal limit; (5) patients with cholecystitis or biliary obstruction; (6) patients with renal failure or undergoing renal dialysis; (7) patients who have had liver or kidney transplants; (8) patients with interstitial lung disease, as observed on a chest x-ray; (9) patients who have experienced post-operative complications; (10) patients with a history of hypersensitivity to any component of the experimental medications or a similar medication class; (11) patients with genetic disorders (Kennedy’s disease, spinal muscular atrophy type 4) or diagnosis of motor neuron disease due to heavy metal poisoning; (12) patients who have received other experimental medications/procedures within 4 weeks of participating in this trial; (13) pregnant women, lactating women, and women of childbearing age who plan on becoming pregnant (i.e., no history of hysterectomy, bilateral tubal ligation, or bilateral oophorectomy within 2 years of menopause) and who do not agree to use medically appropriate contraceptives (e.g., oral medication, hormone implants, intrauterine devices, condoms, or spermicides), or men who do not agree to use appropriate contraceptives with female partners; (14) patients with primary lateral sclerosis and experiencing only upper motor neuron symptoms or with progressive muscular atrophy and experiencing only lower motor neuron symptoms; (15) patients with bleeding diathesis; (16) patients with malignant tumors; (17) patients who have undergone mechanical ventilation or tracheostomy and percutaneous endoscopic gastrostomy; (18) patients with active viral infections (hepatitis B virus antigen, hepatitis C virus antibody, human immunodeficiency virus antibody, cytomegalovirus immunoglobulin M, Epstein–Barr virus immunoglobulin M, herpes simplex virus type 2 immunoglobulin M, syphilis); (19) patients with a conduction block, including chronic inflammatory demyelinating polyneuropathy and multiple sclerosis; and (20) patients deemed by a clinical research investigator to be inappropriate for participation in the clinical trial.

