#### Criteria for discontinuing the allocated interventions

The withdrawal criteria are (1) withdrawal of consent by patients or their agents; (2) use of the medication no longer possible due to adverse events or abnormal findings on laboratory tests; (3) an overall compliance rate of less than 80% during the medication period; (4) a violation of the inclusion/exclusion criteria confirmed during the clinical trial; (5) use of combination medication unavoidable; (6) impossible follow-up; and (7) judgment that the trial is difficult to continue by any investigator.

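### The adverse-event definition turns on whether a finding was seen before the trial, so a baseline abnormality that worsens on treatment falls outside the adverse-event counts

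*Protocol article*

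**What the plan says.** The Adverse events section defines the term in one sentence: "All undesirable medical findings that have not been observed prior to the clinical trial will be classified as adverse events". The next sentence concerns recording: "All unexpected responses related to Mecasin and riluzole will be recorded". The section then covers reporting of serious events ("If serious adverse events occur, these will be notified to the sponsor", followed by the other bodies to be told) and the analysis: "The number of adverse events in the two Mecasin groups will be compared", by a χ² or Fisher's exact test.

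Other statements in the article bear on the same matter:

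- Abstract, Methods: "The frequencies of total adverse events and serious adverse events will be described and documented".
- Table 1: the row "Adverse events assessment" is ticked at weeks 4, 8, 12 and 16.
- Secondary objectives: safety monitoring of Mecasin with standard treatment is a stated aim.
- Exclusion criteria, item 4: among the liver-related exclusions is "aspartate transaminase/alanine transaminase greater than three times the upper normal limit", so smaller elevations do not by themselves exclude a patient.
- Criteria for discontinuing the allocated interventions, item 2: "use of the medication no longer possible due to adverse events or abnormal findings on laboratory tests".

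**The concern.** Whether something counts as an adverse event depends here on whether the finding was seen before the trial. A change in its severity or frequency is not mentioned anywhere in the article.

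That matters in this population. Every participant enters with a progressive disease, takes riluzole and is examined at screening and baseline with blood tests, spirometry and vital signs, plus an electrocardiogram at screening. Many abnormalities can therefore be on record before treatment starts. The more thorough the baseline work-up, the more findings the definition removes from later counting.

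The trial is meant to inform the choice of dose, and adverse-event numbers are to be compared between the two dose groups. If Mecasin aggravates abnormalities that are already present, and does so more at one dose, that comparison would not show it. Absolute harm would be understated even if the gap were the same in all arms.

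**Working it through.** The article states no figure on this point, so the check is a reading of the safety statements against each other.

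**1. What the definition admits.** Take a participant whose alanine transaminase is 2 times the upper normal limit at screening. Item 4 of the exclusion criteria does not exclude this value, since 2 is below 3. Suppose it reaches 8 times the limit at week 8. (Both values are invented for illustration.)

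- If the finding is raised transaminase, it was observed before the trial and the change is not an adverse event.
- If the finding is transaminase at 8 times the limit, it was not observed before and the change is an adverse event.

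The article does not choose between these readings. The first is the plainer one, because nothing in the definition refers to degree.

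**2. Whether something else captures the change.**

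| Type of worsening | Listed outcome? | In the adverse-event count, read literally? |
|---|---|---|
| Function, including bulbar and breathing items | Yes, K-ALSFRS-R | No |
| Limb strength | Yes, MRC scale | No |
| Lung function, creatine kinase, body weight | Yes | No |
| Liver enzymes | No | No |
| Electrocardiogram | No | No |

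For the first three rows the worsening is measured at the treatment visits, although not as an adverse event. For the last two rows no listed outcome picks it up. Table 1 schedules blood tests at every visit through week 12, and the withdrawal criterion on laboratory abnormalities is not limited to new ones. A large change could therefore be seen and could end treatment. That still would not place it in the adverse-event count, and a change that did not end treatment would leave no mark in that count. At the week 16 follow-up, adverse-event assessment is the only procedure in Table 1, so after week 12 the outcome scales offer no second route.

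**3. Where the count is used.** The Abstract promises frequencies of all adverse events, and the Adverse events section compares their number between the Mecasin groups. Both inherit the definition.

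**4. Whether recording is restricted.** The recording sentence says that all unexpected related responses are recorded. It does not say that only these are. The Abstract, Table 1, the group comparison and the reporting of serious events carry no limit by expectedness or relation. Taken together they are compatible with recording everything. The weakness is that this is the only sentence in the section that says what is recorded, and it names a subset.

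**5. Scale.** With 12 participants per arm, one participant with an uncounted event changes the arm's proportion by 1/12 = 0.083, or 8.3 percentage points. This is what any single participant contributes to an arm of that size. The documents do not say how many participants will enter with abnormalities or how many will worsen, so no expected undercount can be calculated.

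**The case against.** A reader might infer more than the text supports, in three ways.

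*That only unexpected and related responses are recorded, in contradiction of the Abstract, with causality decided before an event is written down.* This needs the word only, which the sentence does not contain, and every other safety statement is unrestricted. What remains is an ambiguity that a coordinator could resolve the wrong way.

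*That worsening weakness, swallowing or breathing goes unmeasured.* It does not: the K-ALSFRS-R, the MRC scale and spirometry follow these through week 12. The point is confined to the adverse-event count and bites hardest where no outcome scale applies.

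*That a pre-existing condition can never become an adverse event.* The article speaks of findings, and a much higher value could fairly be called a new finding. The definition also says what will be classified as an adverse event, without saying that nothing else will be. So the loss follows from the literal reading and is not certain in practice.

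Two further objections deserve weight. First, this is a condensed article, and operational rules on baseline abnormalities may stand in the full protocol. That would excuse silence. Here, however, a definition is given, and it is too narrow as given. Second, counting every worsening would turn ordinary ALS decline into an adverse event in all arms, duplicate the primary outcome and dilute the dose comparison. That objection stands, and the fix has to deal with it. The liver example is also narrowed by the exclusion of cirrhosis, hepatic cancer and active hepatitis, though milder elevations remain eligible.

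**Conclusion.** The point holds for the definition. As written, it covers findings not seen before the trial and leaves out worsening of those already present, so the counts in the Abstract and in the group comparison can understate harm. This rests on the literal reading of one sentence and on the article containing no other definition.

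The point does not extend to a restriction on recording. The sentence on unexpected related responses is loosely worded and should be reconciled with the Abstract, but no contradiction is shown. Nor do the documents show that reporting of serious events is affected. That would follow only if serious events are taken as a subset of events meeting this definition, which the article does not state.

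The size of the undercount is unknown, and the 8.3 points per participant is illustrative. The correction is still worth making, because safety is a stated objective, the arms are small and the change is cheap.

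**What to change.** Replace the definition with wording to this effect:

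> An adverse event is any undesirable medical finding that is new, or that worsens in severity or frequency from baseline, whatever its expectedness or its relation to treatment.

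Replace the recording sentence with a statement that all adverse events are recorded, and that relation and expectedness are assessed afterwards.

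Add a rule, set in advance and applied without knowledge of the allocated arm, that decline typical of ALS and already captured by the outcome scales is tabulated separately, so that it does not swamp the comparison of adverse events.

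The cost is a few sentences and a note to the coordinators. The downside is more adverse-event forms and higher counts in every arm. The rule separating typical decline from other worsening also needs some judgement to write.

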### Secondary objectives

The secondary objectives are to determine whether Mecasin, combined with standard ALS treatment, significantly slows the rate of functional deterioration in patients with ALS over 12 weeks, compared with standard treatment alone, and to monitor the safety of Mecasin combined with standard ALS treatment over 16 months. We also aimed to determine whether this treatment affects health-related quality of life, depression, muscle strength, pain, fatigue, pulmonary function, creatine kinase, or body weight in patients with ALS over 12 months.

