### Design and setting

This will be a phase II-A, multi-center, randomized, double-blind, placebo-controlled trial. All patients will have taken riluzole for more than 3 months before screening and will be committed to take riluzole during trials. The trial will be conducted at South Korea Wonkwang University Gwangju Hospital and Sanbon Hospital. The flow diagram of the trial is shown in Fig. 1. We will test the effects of 1.6 g and 2.4 g of Mecasin to investigate optimal dosage and treatment efficacy. The schedule of study procedures is depicted in Fig. 2 and details are provided in Table 1.

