## Discussion

There are large variations in the reported annual incidence of ALS in Europe, Asia, and North America, ranging from 2.1 to 8.5 per 100,000 population [26]. There is currently no known method for a permanent cure for ALS using conventional medicine [27]. Thus, patients with ALS may attempt to visit a multidisciplinary clinic or use complementary and alternative medicine [28, 29].

Prior studies have shown that Mecasin, a herbal extract, has neuro-protective and anti-neuroinflammatory effects, and its safety has been proven in both in vitro and in vivo trials [8–14]; it has been shown to reduce the progression of ALS in Korean Medicine Clinics [6, 7]. No previous randomized controlled trial has examined the effects of Mecasin for the treatment of ALS. The planned clinical trial will determine the optimal dosages of Mecasin and will show whether combined Mecasin and riluzole treatment is both effective and safe for patients with ALS Additional file 1.

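### The only stated adverse event comparison is between the two Mecasin doses, so it leaves out placebo and has no power for a harm common to both; as worded, it also tests events, not patients.

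*Protocol article*

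**What the plan says.** The Adverse events section of the protocol article contains one between-group safety analysis: "The number of adverse events in the two Mecasin groups will be compared using the" chi-square or Fisher's exact test. It names two groups, both on Mecasin, and the quantity tested is the number of events.

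The other relevant statements are:

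- **Abstract, Methods:** "The frequencies of total adverse events and serious adverse events will be described and documented". No arm is named or excluded, and no comparison is stated.
- **Design and setting:** a "phase II-A, multi-center, randomized, double-blind, placebo-controlled trial".
- **Riluzole:** every participant takes riluzole, so the placebo arm is standard treatment alone.
- **Secondary objectives:** one aim is "to monitor the safety of Mecasin combined with standard ALS treatment".
- **Discussion:** the trial "will show whether combined Mecasin and riluzole treatment is both effective and safe for patients with ALS".
- **Table 1:** adverse events are assessed at weeks 4, 8, 12 and 16, with no arm excepted.
- **Statistical analysis:** the efficacy analyses of covariance compare all the randomised groups, for the primary and the secondary outcomes.

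**The concern.** The safety question in the objectives and the Discussion is whether Mecasin added to riluzole causes harm that riluzole alone does not. The randomised contrast for that question is Mecasin against placebo. The stated test compares one dose of Mecasin with the other, so it answers a different question: whether harm differs between 1.6 g and 2.4 g. A toxicity that both doses cause to the same degree gives no signal in that test, and the null result could be reported as reassurance.

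The background makes the control arm more important here. The article counts every new undesirable medical finding as an adverse event, so events that come from ALS itself or from riluzole are included. The concurrent placebo arm is what separates these from an effect of Mecasin.

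The second issue is the unit of analysis. Chi-square and Fisher's exact tests need independent units. With four assessments, one patient can contribute several events, and these are not independent.

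**Working it through.** **Inputs.** From the article: three arms, 1:1:1 allocation, 12 patients per arm (3 × 12 = 36). The article gives no adverse event rates, no significance level and no number of events per patient. Event rates, a two-sided 5% level and event-count distributions below are therefore assumptions. The plan states no safety figure to reproduce. Steps 1 to 3 count patients with at least one event; step 4 takes the wording literally and counts events. They examine two alternative readings of the same sentence, so their results should not be combined.

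**Step 1: power of the stated contrast for a common harm.** Let both doses have the same probability p that a patient has an event. Summing the binomial probabilities of all 12 v 12 tables with Fisher p ≤ 0.05 gives:

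| Shared rate p | Probability of rejection, 1.6 g v 2.4 g |
|---|---|
| 30% | 0.017 |
| 50% | 0.023 |
| 60% | 0.021 |
| 70% | 0.017 |
| 80% | 0.012 |

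The placebo rate does not enter the calculation. These values are the type I error of the dose comparison, so it has no power for a harm common to both doses, however large.

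**Step 2: what the omitted contrast could show.** Same method, with Mecasin pooled (24) v placebo (12), and one dose v placebo (12 v 12):

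| Mecasin v placebo rate | Pooled v placebo | One dose v placebo |
|---|---|---|
| 50% v 10% | 0.65 | 0.42 |
| 70% v 10% | 0.95 | 0.83 |
| 60% v 20% | 0.58 | 0.39 |
| 80% v 20% | 0.92 | 0.81 |
| 60% v 30% | 0.32 | 0.21 |
| 80% v 30% | 0.77 | 0.61 |

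The pooled contrast is informative for large harms and weak for moderate ones.

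**Step 3: one illustration.** Suppose 5/12 patients on 1.6 g and 6/12 on 2.4 g have an event. The dose comparison gives Fisher p = 1.00. Pooled Mecasin is 5 + 6 = 11 of 24. Against placebo:

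| Placebo | Fisher p, 11/24 v placebo |
|---|---|
| 0/12 | 0.0059 |
| 1/12 | 0.031 |
| 2/12 | 0.14 |
| 3/12 | 0.29 |

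The dose comparison stays at 1.00 in every row. The pooled result depends heavily on the placebo count.

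**Step 4: events as units.** Let a and b be the total events in two identical arms of 12. Treating events as independent, the 1:1 chi-square statistic is (a − b)²/(a + b), rejected above 3.84. If counts per patient are negative binomial with mean m and dispersion k, their variance is m(1 + m/k). The statistic is then too large by a factor of about 1 + m/k. With m = 1.5 (assumed), simulation gives:

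| Dispersion k | 1 + 1.5/k | Type I error |
|---|---|---|
| none (Poisson) | 1.00 | 5% |
| 10 | 1.15 | about 7% |
| 5 | 1.30 | about 8% |
| 2 | 1.75 | about 14% |
| 1 | 2.50 | about 21% |
| 0.5 | 4.00 | about 32% |

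An exact binomial split of the events behaves in the same way: with a mean of 2 events, the type I error is 0.04 without heterogeneity and 0.14, 0.22 and 0.34 at k = 2, 1 and 0.5. The direction is certain once patients differ enough in their tendency to have events; the size is not.

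**The case against.** **Placebo may still be reported.** The abstract's descriptive frequencies exclude no arm, and adverse events are assessed in all of them. A reader might infer that the placebo arm goes unused for safety, or that a common harm could not be detected at all. The article supports neither. Placebo is left out of the only stated comparison, and a descriptive table by arm could still reveal a common harm; 5/12, 6/12 and 0/12 would be plain to see. This objection stands and limits the point to the test and to what may be concluded from it.

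**Condensed article.** A full plan could add a placebo comparison. But the published sentence does not merely omit detail: it names the two groups to be compared, while the efficacy sections of the same article name all of them.

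**Dose finding is the primary aim.** A comparison of 1.6 g with 2.4 g is relevant to it. That is a reason to keep the comparison, not to make it the only one.

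**Loose wording on events.** A total event count has no natural cell for non-events, so naming chi-square and Fisher's tests suggests that patients with an event may have been meant. That is fair. A reader might infer that the planned p-value is certainly wrong, or that its error rate is 14% to 32%. Those figures need the literal reading and strong overdispersion; with mild heterogeneity the inflation is small. What stands is that the sentence must name its unit.

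**Small numbers.** Power of 0.21 to 0.32 at 60% v 30% means that a null test against placebo could also be misread as safe, and many tests in 36 patients would need a multiplicity position. This stands, and it is why the fix puts estimates first.

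**Conclusion.** Wrong as written. The only adverse event comparison that the article specifies leaves out the randomised riluzole-alone arm. For a harm common to both doses, it rejects at no more than its own type I error (0.012 to 0.023 at shared rates of 30% to 80%), so it cannot support the Discussion's expectation about the safety of the combination. This conclusion follows from the choice of groups and does not depend on any assumed placebo rate.

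The gain from adding placebo does depend on assumed rates: pooled power runs from 0.32 to 0.95 over the cases shown. The small p-value of 0.0059 in the illustration needs zero placebo events.

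The unit of analysis is a secondary part of the point. If events are counted, the type I error exceeds the nominal level when patients are heterogeneous, from about 7% at mild to about 32% at strong overdispersion with an assumed mean of 1.5 events. If patients are counted, this part falls away and only the wording needs correcting.

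**What to change.** Replace the comparison sentence in the Adverse events section with text to this effect:

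*The number and percentage of patients with at least one adverse event, and with at least one serious adverse event, will be reported for all three arms. Risk differences with exact 95% confidence intervals will be given for pooled Mecasin versus placebo and for each dose versus placebo. Pooled Mecasin and placebo will be compared by Fisher's exact test on patients; 1.6 g versus 2.4 g is a further comparison. All comparisons are exploratory, without multiplicity adjustment, and a non-significant result will not be taken as evidence of safety. Event counts are descriptive.*

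The cost is a revised sentence and a few more table columns. No new data are needed, because adverse event assessment is already scheduled for all participants. The intervals will be wide with 12 patients per arm, and the report should say so.
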